#### Intervention description {11a}

In the active group, subjects consume daily 3 g of a sugar-free rusk-like biscuit powder, which contains small amounts of cow’s milk, hen’s egg, peanuts, and/or hazelnuts separately, corresponding to their sensitization(s). Therefore, a child may receive only one or up to four foods, each offered in a separate study powder. The allergen dose in each study product will be around 2 mg of food protein (Table 1).

**Table 1 Tab1:** Allergen amount in study product

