### Outcomes {12}

#### Primary endpoint

The primary endpoint is IgE-mediated food allergy to the target food (hen’s egg, cow’s milk, peanuts, or hazelnuts), after 3–6 months of intervention (plus max. 3 months in case of postponed oral food challenge). For polyvalent-sensitized children, a “primary target food allergen” will be determined randomly at enrollment which will be used to define the primary endpoint.

The presence of IgE-mediated food allergy is defined by either of the following (Table 2):Positive oral food challenge (plus sIgE ≥ 0.1 or positive skin prick test)An immediate-type allergic reaction due to an accidental exposure (plus sIgE ≥ 0.1 or positive skin prick test)

**Table 2 Tab2:** Diagnosis of food allergy for the determination of endpoints

Procedure	Positive result
**Oral food challenge (OFC)**	OFC outcome is positive if objective symptoms of immediate type allergic reactions occur after any administered dose. (OFC outcome is negative if no objective symptoms of immediate type allergic reactions occur after ingestion of any administered dose.)
**Allergen-specific IgE (sIgE)**	sIgE ≥ 0.1 kU/l
**Skin prick test (SPT)**	Wheel size ≥ 3 mm
**Immediate-type allergic reaction due to accidental exposure**	Parent-reported objective symptoms of immediate type allergic reactions upon accidental exposure to the interventional food(s) during the interventional period

OFC, sIgE determination (blood sampling), and skin prick test (SPT) are performed onsite on the day of the scheduled visit (V2), which should be 3–6 months (plus max. 3 months in case of postponed oral food challenge) after the start of the intervention (V1). Specific IgE and/or SPT at baseline must be assessed no longer than 3 months prior to enrollment.

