#### Secondary endpoints

The following secondary endpoints will be assessed after 3–6 months (plus max. 3 months) of intervention (V2):IgE-mediated food allergy determined by OFC (plus sIgE ≥ 0.1 or positive SPT) to the “primary target food allergen”IgE-mediated food allergy determined by an immediate-type allergic reaction due to accidental exposure (plus sIgE ≥ 0.1 or positive SPT) to the “primary target food allergen”IgE-mediated food allergy determined by OFC (plus sIgE ≥ 0.1 or positive SPT) or an immediate-type allergic reaction due to an accidental exposure (plus sIgE ≥ 0.1 or positive SPT) to either of the following (for children sensitized to the respective allergen at baseline):Hen’s eggCow’s milkPeanutsHazelnutsOccurrence (frequency and severity) of immediate type allergic symptomsOccurrence of gastrointestinal symptomsMultiple food allergiesNumber of food allergiesChange to baseline of SCORAD (in subjects with eczema)Change to baseline of EASIscore (in subjects with eczema)WheezingAllergen-specific IgE to hen’s egg, cow’s milk, peanuts, and/or hazelnutsWheal size measured by skin prick testing to hen’s egg, cow’s milk, peanuts, and/or hazelnuts

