### Assignment of interventions: allocation

#### Sequence generation {16a}

After enrollment performed by the study investigators, participants will be randomly assigned to receive verum or placebo. The randomization will be prepared by the trial statistician and will be implemented within the REDCap database system by the data manager. Children will be randomized to receive verum or placebo (1:1 allocation ratio) for each food allergen against which the child is sensitized.

Randomization will be performed in blocks (with varying block lengths) and will be stratified by the following:Primary allergen (cow’s milk, hen’s egg, peanuts, or hazelnuts)Age (≤ 2 vs. > 2 years of age)Grade of sensitization to the primary food allergen (low vs. medium vs. high) defined by either of the following:
◦ Specific IgE levels of the primary food allergen, according to the following CAP classes:Low: IgE ≥ 0.10 ≤ 3.50 (CAP 0–2)Medium: IgE > 3.50 ≤ 50.0 (CAP 3 and 4)High: IgE > 50.0 (CAP 5 and 6)◦ According to skin prick test results of the primary food allergen (in case of missing specific IgE values)
Low: wheal size ≥ 3 mm ≤ 5 mmMedium: wheal size > 5 mm ≤ 9 mmHigh: wheal size > 9 mmPlanned duration of intervention, determined by the date of the routinely scheduled OFC (< 5 vs. ≥ 5 months)

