## Statistical methods

### Statistical methods for primary and secondary outcomes {20a}

The primary analysis of the primary endpoint will be performed by logistic regression with (fixed) factor treatment group (verum, placebo regarding the primary allergen) and the stratification factors primary allergen (hen’s egg, cow’s milk, peanuts, hazelnuts), age group (≤ 2, > 2 years of age), grade of sensitization (low, medium, and high), and planned duration of intervention (< 5, ≥ 5 months). In case of stratification groups with very few cases, stratification groups may be combined (e.g., low vs. medium/high grade of sensitization) or the factor omitted from the analysis model; the decision will be finalized, blinded, and described in the statistical analysis plan (SAP). From this model, the odds ratio for verum vs. placebo treatment will be calculated with a 95% confidence interval and a *p*-value for the treatment group comparison. The analysis will be performed on the full analysis set (FAS) based on the intention-to-treat principle without imputation of missing values. The significance level will be set to 0.05 (two-sided). All other analyses will be considered explorative. Several explorative sensitivity analyses will be performed for the primary endpoint: a re-run of the primary analysis model with the per-protocol population (instead of the FAS). In case of relevant differences between the treatment groups with respect to baseline variables, the primary analysis will be repeated with further adjustment variables (FAS population). To account for the potentially varying lengths of follow-up, a Cox proportional hazards regression as well as Poisson regression will be used to analyze the primary endpoint. Explorative analysis of secondary endpoints will follow the same principle as the primary analysis of the primary endpoint, i.e., models with the (fixed) factor treatment group and the stratification factors. Binary endpoints will be analyzed by logistic regression; continuous endpoints will be analyzed by analysis of covariance (ANCOVA) with the respective baseline value (if available) as an additional covariate. Secondary endpoints will be analyzed with the FAS. Regarding safety endpoints, the nature, frequency, and severity of adverse events and safety variables, including serious adverse events, will be summarized descriptively by treatment group (based on the safety population of all participants who received at least one dose of study treatment and have at least one post-baseline safety assessment, analyzed according to the treatment received). Further details will be described in the SAP, which will be finalized prior to data analysis.

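### The models for number of food allergies and multiple food allergies leave out how many target foods the child is sensitised to, which costs precision

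*Protocol article*

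**What the plan says.** All places are in the protocol article.

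- **Secondary models, section {20a}.** Secondary endpoints follow the principle of the primary analysis: "models with the (fixed) factor treatment group and the stratification factors". Binary endpoints get logistic regression. For the rest, "continuous endpoints will be analyzed by analysis of covariance (ANCOVA) with the respective baseline value (if available) as an additional covariate". The treatment factor is "treatment group (verum, placebo regarding the primary allergen". On status: "All other analyses will be considered explorative". Further detail is deferred to the SAP.
- **Stratification factors, section {16a}.** These are primary allergen, age group, planned duration and "Grade of sensitization to the primary food allergen (low vs. medium vs. high".
- **Choice of the primary food, Primary endpoint.** In polysensitised children the primary target food "will be determined randomly at enrollment which will be used to define the primary endpoint".
- **Number of foods per child, section {11a}.** "a child may receive only one or up to four foods".
- **Endpoints, Secondary endpoints.** Allergy to each single food is restricted ("for children sensitized to the respective allergen at baseline"). Multiple food allergies and number of food allergies are listed without such a restriction.

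**The concern.** The challenge at visit 2 is against the child's target food or foods. A child sensitised to one food can hardly accumulate several food allergies within the trial, while a child sensitised to four can. The number of sensitised foods therefore sets most of the room in which both endpoints can move. It is a baseline quantity, known before randomisation, and it decides which powders the child receives. Yet it is neither a stratification factor nor a covariate.

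For the single-food endpoints the plan does account for who is at risk, by restricting the population. It does not carry this over to the count or to multiple food allergies. The development of multiple food allergies is a named secondary objective (section {7}), so the efficiency of these two analyses matters even though they are exploratory.

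A smaller question concerns the food-specific models. The only grade among the stratification factors is that of the primary food. In the hen's egg model, a child sensitised to egg and peanut whose drawn primary food is peanut is adjusted for the peanut grade.

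**Working it through.** **1. The plan's own figure.** Inputs from section {14}: 35% vs 60%, two-sided 5%, 80% power, dropout about 10%.

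n per arm = [1.960·√(2·0.475·0.525) + 0.842·√(0.35·0.65 + 0.60·0.40)]² / 0.25² = (1.384 + 0.575)² / 0.0625 ≈ 61.4, so 62.

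Power at 62 per arm is 80.4%. With dropout, 124/0.90 = 137.8, so 138. The figure reproduces, and nothing below changes it. The protocol states no power for secondary endpoints.

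**2. Is the number of foods in the model by another route?** The model terms are treatment, primary allergen, age group, grade for the primary food and planned duration, plus the endpoint's own baseline value in ANCOVA. None of these is the number of sensitised foods, k.

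**3. Cost for the number of food allergies.** The documents do not give the distribution of k or the within-child correlation. Both are assumptions here.

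*Simulation A.* 1,500 trials, 62 per arm; 40/30/20/10% of children with 1/2/3/4 foods; per-food risk 35% vs 60%; child random effect with SD 1.5 on the logit scale; linear model on arm, without and with k.

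*Simulation B.* 700 trials per scenario, n = 124; primary food and primary-food grade in both models; grades correlated 0.3 between foods; grade effect on allergy; all of a child's foods on the same arm; per-food log odds ratio ln(0.35/0.65) − ln(0.60/0.40) = −1.02. Age and duration were not simulated.

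| Scenario (shares with 1/2/3/4 foods) | Mean k | SE or SD without k | with k | Reduction | Power without k | with k |
|---|---|---|---|---|---|---|
| A: 40/30/20/10 | 2.0 | 0.170 | 0.148 | 13% | 82% | 91% |
| B: 40/30/20/10 | 2.0 | 0.151 | 0.125 | 17% | 82% | 93% |
| B: 60/25/10/5 | 1.6 | 0.138 | 0.112 | 19% | 76% | 89% |
| B: 25/25/25/25 | 2.5 | 0.168 | 0.139 | 17% | 89% | 97% |

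- Reduction = 1 − (with/without), for example 1 − 0.112/0.138 = 18.8%.
- Share of variance removed = 1 − (with/without)²: from 1 − (0.148/0.170)² = 24% to 1 − (0.112/0.138)² = 34%.
- Sample-size equivalent = (without/with)²: from (0.170/0.148)² = 1.32 to (0.138/0.112)² = 1.52. Leaving k out costs what about 32 to 52% more children would buy for this endpoint.

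**4. Bias and type I error.** In B with mean k = 2.0 the mean effect is −0.446 without k and −0.445 with it. With no effect, the count models reject in 4.1 to 6.6% of trials. The Monte Carlo standard error is √(0.05·0.95/700) = 0.8 points, so this is compatible with 5%.

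**5. The grade in the food-specific models.** If the foods are equally common and the primary food is drawn evenly, a child with k foods enters a given food's model with probability k/4, and that food is the child's primary food with probability 1/4. The share carrying another food's grade is 1 − 1/mean(k):

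- mean k = 1.6: 38%
- mean k = 2.0: 50%
- mean k = 2.5: 60%

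Replacing it in B by the grade of the food analysed moves power from 38% to 37%, 45% to 47% and 50% to 54% respectively. These logistic comparisons leave out trials in which the model did not fit or gave an extreme estimate (2 to 34 of 700 per model with an effect present), so small differences should not be read closely.

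**The case against.** The strongest reply is that this is SAP business. The article is an abridged protocol, the analyses are exploratory, adjusting for the randomisation strata is conventional and valid, and the SAP is promised. That lowers the weight of the point but does not remove it. Section {20a} states a rule for the secondary models, and a SAP that follows it would inherit the omission.

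A second reply is that the size rests on inputs the documents do not give. That is true. The direction was the same in every scenario tried, but the figures are ranges under assumptions.

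Four stronger readings are tempting, and the documents do not support them:

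- **That the secondary estimates are biased or the tests invalid.** Treatment is randomised, so k is balanced in expectation. Step 4 shows neither bias nor type I error inflation.
- **That the wrong-food grade spoils the food-specific results.** It concerns only polysensitised children whose drawn primary food is another one, and power hardly changes. Specific IgE and wheal size, as continuous endpoints, also receive their own baseline value where available.
- **That k is the largest source of variation in the count.** It accounts for about 24 to 34% of the variance under the assumptions, and no other source was compared.
- **That a fixed share of children are structural zeros for multiple food allergies.** Any such share merely restates the assumed proportion with one sensitised food. The protocol sets no baseline restriction on this endpoint, repeats skin prick tests for all four foods at visit 2 and records reactions to other foods. A second allergy in a child sensitised to one food is unlikely but not excluded.

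**Conclusion.** The point holds as one of efficiency. The stated models for number of food allergies and multiple food allergies omit a baseline variable that the trial already has and that largely bounds both outcomes. For the count, including it reduces the SE or SD of the treatment effect by about 13 to 19% and adds about 8 to 13 percentage points of power. This rests on an assumed mean of 1.6 to 2.5 foods per child, an assumed within-child correlation, and all foods of a child being on the same arm. Section {16a} speaks of allocation for each food allergen; if arms could differ between a child's foods, these figures would not apply.

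No comparable gain from adding k was computed for multiple food allergies. There the argument rests on the same bounding and on interpretability. The grade mismatch in the food-specific models is a matter of coherence only.

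**What to change.** In the SAP, before unblinding:

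1. Add the number of target foods sensitised at baseline (1 to 4) as a covariate in the models for number of food allergies and multiple food allergies. Keep all stratification factors.
2. Report multiple food allergies additionally among children sensitised to at least two target foods, alongside the full analysis set result.
3. If a per-food proportion is wanted as a supplement, divide by baseline-sensitised foods. Challenged foods are determined after randomisation and are unsuitable as a denominator. The proportion is a different estimand from the count and should not replace it.
4. In each food-specific allergy model, add the baseline grade of the food analysed. Do not remove the primary-allergen factor or the primary-food grade, since both are randomisation strata.

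The cost is SAP wording. Sensitisation to the target foods is already established at baseline for eligibility and for choosing the powders. The models gain one or a few parameters, and the additional analysis in item 2 has a smaller denominator. If the grade in item 4 makes a small food-specific model unstable, the pooling of sparse categories that section {20a} already allows for the primary model can be applied.

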### Eligibility criteria {10}

Infants and children aged 8 months to 4 years with a sensitization (specific IgE (sIgE) ≥ 0.1 kU/l and/or skin prick test (SPT) wheal size ≥ 3 mm) against cow’s milk, hen’s egg, peanuts, and/or hazelnuts (target allergenic foods) and an already scheduled oral food challenge at the Charité – Universitätsmedizin Berlin (3–6 months after enrollment) for routine diagnostics are eligible for the trial. Infants are excluded from the study if they have previously consumed the target allergenic food they are sensitized to in relevant amounts. Further exclusion criteria are wheat allergy (study product contains wheat), severe other health issues (e.g., heart disease), a twin sibling already taking part in the study, and participation in another interventional trial.

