#### Participant timeline {13}

During the screening visit (V1), the participation criteria will be checked, and information on demographics, subject/family characteristics, relevant medical history, medication, and nutrition will be recorded. In addition, anthropometric measurements and a physical examination will be performed including the assessment of the severity of eczema (in case of eczema). Skin swabs and stool and saliva samples will be collected. Blood will be collected, or a skin prick test (SPT) will be performed, if the child’s sensitization status was assessed ≥ 3 months prior to V1. Transepidermal water loss (TEWL) will be measured, and palmar hyperlinearity will be determined. Parents are asked to collect a dust sample from the bed and living room within 24 h prior to both study visits. Eligible children will be randomized to one of the two study groups. The first feeding of the study product will be performed at the study site. The study product will be dispensed. Parents will be asked to fill out a (e-)diary for the entire study period (from V1 to V2). Two weeks after V1, parents will be called (PC1) to review compliance, tolerance of the study product, and adverse events. The study product will be consumed daily until an oral food challenge in routine diagnostics at V2 will be performed after their individual waiting time of 3–6 months. At V2, information on medical history, medication, and nutrition will be recorded. In addition, anthropometric measurements and a physical examination will be performed. Skin swabs and stool and saliva samples will be collected. TEWL will be measured. A blood sample will be collected, and a SPT with cow’s milk, hen’s egg, peanuts, and hazelnuts will be performed. Oral food challenges will be performed according to standardized procedures in a double-blinded placebo-controlled manner (Table 3).

**Table 3 Tab3:** Study visits and procedures

	**Visit 1 (V1)**	**Phone call 1 (PC1)**	**Visit 2 (V2)**
Time	0 weeks, baseline	2 weeks (± 5 days) after V1	3–6 months after V1 ± 14 days
Informed consent	x		
Check eligibility	x		
Randomization	x		
Demographics/subject characteristics	x		x
Family characteristics	x		x
Medical history	x		x
Review adverse events (AEs)		x	x
Review concomitant medication	x	x	x
Nutritional characteristics	x		x
Physical examination	x		x
SCORAD, EASIscore (in case of eczema)	x		x
Transepidermal water loss measurement (TEWL)	x		x
Palmar hyperlinearity	X		
Skin prick testing	(x)^a^		x

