Skin swabs	x		x
Saliva sampling	x		x
Stool sampling	x		x
Dust sampling	x		x
Blood sampling	(x)^a^		x
Oral food challenge			x
Dispensation of the study product	x		
Feeding of the study product at the site	x		
Review tolerance study product		x	x

^a^Blood will be collected, or a skin prick test will be performed at V1, if the child’s sensitization status was assessed ≥ 3 months prior to enrollment

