### Methods in analysis to handle protocol non-adherence and any statistical methods to handle missing data {20c}

Selected secondary endpoints will also be analyzed with the per-protocol (PP) population. The PP is a subset of the FAS defined without participants with repeated insufficient consumption of the study product (verum), i.e., consumption < 3 times/week for 3 weeks (either during 3 consecutive weeks or three repeated events of 1 week); OFC taking place before 3 months (after starting the intervention); or OFC taking place after more than 9 months (after starting the intervention). As a general strategy, missing data will not be imputed in this study.

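### Only one of sIgE or skin prick test is required at baseline, yet V2 sIgE and wheal size get a baseline-adjusted ANCOVA with no imputation: by default, children without the matching baseline test drop out of two explorative endpoints

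*Protocol article*

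**What the plan says.** All references are to the protocol article.

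- **Entry (Eligibility criteria {10}).** Sensitization is shown by "specific IgE (sIgE) ≥ 0.1 kU/l and/or skin prick test (SPT) wheal size ≥ 3 mm", so one test is enough.
- **Age of the baseline test (Primary endpoint, under Outcomes {12}).** "Specific IgE and/or SPT at baseline must be assessed no longer than 3 months prior to enrollment". Again, one test suffices.
- **V1 testing (Participant timeline {13}).** "Blood will be collected, or a skin prick test (SPT) will be performed", but only when the existing result is at least three months old. The footnote to Table 3 has the same either/or.
- **V2 testing (same section).** "A blood sample will be collected, and a SPT with cow’s milk, hen’s egg, peanuts, and hazelnuts will be performed". Both tests are due in every child.
- **Stratification (Sequence generation {16a}).** Grade of sensitization is defined by sIgE, with the skin prick test used when sIgE is missing. The plan therefore expects some children to have no baseline sIgE.
- **Endpoints (Secondary endpoints).** Allergen-specific IgE and wheal size to the four foods at V2 are both listed.
- **Model (section {20a}).** Continuous endpoints are analysed by "analysis of covariance (ANCOVA) with the respective baseline value (if available) as an additional covariate", together with treatment group and the stratification factors, in the full analysis set. All analyses other than the primary are explorative.
- **Missing data (section {20c}).** "As a general strategy, missing data will not be imputed in this study".

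**The concern.** Each rule is reasonable alone, but for these two endpoints they do not fit together. An ANCOVA cannot use a child whose covariate value is missing unless something is put in its place, and the stated strategy is to put nothing in. A child who entered on a skin prick test alone has a V2 sIgE and no baseline sIgE; a child who entered on sIgE alone has a V2 wheal and no baseline wheal.

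If the covariate is kept, an analysis labelled as full analysis set would quietly become an analysis of children who had the matching test at baseline. The sIgE and wheal-size results would then rest on partly different children. Measured V2 outcomes would be discarded, and unnecessarily so, since established methods keep them.

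**Working it through.** **No figure in the plan to reproduce.** The only sample-size calculation (62 per group, 124 analysed, 138 randomized) is for the primary endpoint. It reproduces: 35% vs 60%, two-sided 5%, 62 per group gives 80.4% power. It does not bear on this point. sIgE and wheal size are listed by food, so 124 need not be the number behind either endpoint, and no count of lost children is derived from it.

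**Step 1: what the model does by default.** In a simulated data set of 124 children (an arbitrary size), 67 had a baseline value. The ANCOVA with the baseline covariate used 67 observations; the same model without it used all 124.

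**Step 2: the readings of the proviso on availability.**

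| Reading | Children with a V2 value | Baseline adjustment |
|---|---|---|
| Covariate kept wherever the endpoint has a baseline | those lacking the matching test are excluded | full |
| Covariate omitted for everyone | all kept | only through the sensitization-grade stratum |
| Covariate used for some children and not others | all kept | needs a filled-in value or an indicator, and neither is named |

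**Step 3: size of the loss.** Two inputs are not in the documents and are assumed:

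- m, the share of children without the matching baseline test: 20–50%.
- ρ, the correlation between baseline and V2 values, read as what remains after the stratification factors: 0.6–0.8.

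With the unadjusted all-children variance of the treatment effect set to 1, and missingness unrelated to arm:

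- complete-case ANCOVA: (1−ρ²)/(1−m)
- model keeping all V2 values: 1/[(1−m)/(1−ρ²) + m]
- ratio of standard errors: √[1 + m(1−ρ²)/(1−m)]

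| m | ρ = 0.6 (1−ρ² = 0.64) | ρ = 0.8 (1−ρ² = 0.36) |
|---|---|---|
| 20% | √(1 + 0.25×0.64) = √1.16 = 1.08 | √(1 + 0.25×0.36) = √1.09 = 1.04 |
| 30% | √(1 + 0.429×0.64) = √1.274 = 1.13 | √(1 + 0.429×0.36) = √1.154 = 1.07 |
| 50% | √(1 + 1×0.64) = √1.64 = 1.28 | √(1 + 1×0.36) = √1.36 = 1.17 |

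The complete-case standard error is thus 4–28% larger over this range. As m goes to 0 the ratio goes to 1.

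**Step 4: when adjusting costs more than it gains.** Complete-case ANCOVA is less precise than leaving the baseline out when (1−ρ²)/(1−m) > 1, that is, when m > ρ². The thresholds are 36% at ρ = 0.6 and 64% at ρ = 0.8.

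**Step 5: check on the simpler remedy.** ANCOVA with a mean-filled baseline and an indicator, fitted with one residual variance, has relative variance (1−m)(1−ρ²) + m = 1 − (1−m)ρ². At m = 20%, ρ = 0.6 this is 1 − 0.8×0.36 = 0.712, against 0.64/0.8 = 0.80 for complete cases: a gain. At m = 20%, ρ = 0.8 it is 1 − 0.8×0.64 = 0.488, against 0.36/0.8 = 0.45: a small loss. Letting the residual variance differ between children with and without a baseline removes this drawback, because each group is then weighted by its own precision, as in the all-data formula of Step 3.

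**The case against.** **The document never says these children are dropped.** This stands. The proviso on availability shows that the authors foresaw missing baselines, and it can be read as omitting the covariate. A reader might infer a written rule that every child without the matching test is excluded; there is none. Exclusion is the default result of the stated model and the general no-imputation strategy.

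**It is detail for the statistical analysis plan.** This stands in part. The article is an abridged protocol, defers further details to that plan, and states no imputation only as a general strategy. But the article itself fixes the either/or baseline, the baseline-adjusted model and the no-imputation strategy, and under either plain reading of the proviso something is lost.

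**Omitting the covariate costs less than it seems.** Correct as far as it goes. The sensitization grade is in the model and is built from baseline sIgE, or from the skin prick test. For the primary allergen, part of the baseline adjustment therefore survives for every child.

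**Selection suggests bias.** A reader might infer that the treatment comparison is biased, because having a test on record depends on work-up before the trial. The documents do not support that. Baseline testing precedes randomization, so its absence cannot by itself differ systematically between arms.

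**The size is hypothetical.** This stands. Using the skin prick test only when sIgE is missing suggests that sIgE is the usual test. The planned separate subgroup analyses by sIgE level and by wheal size are consistent with both often being on record. A share near zero fits the text as well as 20% does.

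**Conclusion.** The point holds as a minor one. For V2 sIgE and wheal size, the stated method either leaves out children with a measured outcome or gives up baseline adjustment beyond the sensitization-grade stratum. The harm is confined to the precision and the population of two explorative secondary endpoints. The primary logistic regression is unaffected, because its grade factor falls back on the skin prick test when sIgE is missing.

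The 4–28% range for the standard error rests wholly on the assumed m of 20–50% and ρ of 0.6–0.8. The documents give neither, and if routine work-up supplies both tests for nearly all children the loss is negligible.

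**What to change.** In the analysis plan, state for these two endpoints that every child with a V2 value is analysed, by one of two methods:

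- a constrained longitudinal model with V1 and V2 values as outcomes, a common baseline mean across arms, and the stratification factors; or
- ANCOVA with a missing baseline filled in by a single value such as the mean, plus a missing-baseline indicator, preferably with separate residual variances for children with and without a baseline.

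The precision figures above apply to the first. The second is simpler and keeps the full population; with a single residual variance it may gain little or no precision when ρ is high and m is small.

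Also state that the no-imputation rule concerns outcomes and not baseline covariates, and report how many children lack each baseline test, by arm.

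The cost is a few sentences, slightly more modelling work and a narrow exception to the general no-imputation strategy. No new measurements are needed.
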